# The Mobile Insulin Titration Intervention (MITI) for Insulin Glargine Titration in an Urban, Low-Income Population: Randomized Controlled Trial Protocol

**DOI:** 10.2196/resprot.4206

**Published:** 2015-03-13

**Keywords:** patient care management, delivery of care, health care disparities, telemedicine, remote consultation

## Abstract

**Background:**

Patients on insulin glargine typically visit a clinician to obtain advice on how to adjust their insulin dose. These multiple clinic visits can be costly and time-consuming, particularly for low-income patients. It may be feasible to achieve insulin titration through text messages and phone calls with patients instead of face-to-face clinic visits.

**Objective:**

The objectives of this study are to (1) evaluate if the Mobile Insulin Titration Intervention (MITI) is clinically effective by helping patients reach their optimal dose of insulin glargine, (2) determine if the intervention is feasible within the setting and population, (3) assess patient satisfaction with the intervention, and (4) measure the costs associated with this intervention.

**Methods:**

This is a pilot study evaluating an approach to insulin titration using text messages and phone calls among patients with insulin-dependent type 2 diabetes in the outpatient medical clinic of Bellevue Hospital Center, a safety-net hospital in New York City. Patients will be randomized in a 1:1 ratio to either the MITI arm (texting/phone call intervention) or the usual-care arm (in-person clinic visits). Using a Web-based platform, weekday text messages will be sent to patients in the MITI arm, asking them to text back their fasting blood glucose values. In addition to daily reviews for alarm values, a clinician will rereview the texted values weekly, consult our physician-approved titration algorithm, and call the patients with advice on how to adjust their insulin dose. The primary outcome will be whether or not a patient reaches his/her optimal dose of insulin glargine within 12 weeks.

**Results:**

Recruitment for this study occurred between June 2013 and December 2014. We are continuing to collect intervention and follow-up data from our patients who are currently enrolled. The results of our data analysis are expected to be available in 2015.

**Conclusions:**

This study explores the use of widely-available text messaging and voice technologies for insulin titration. We aim to show that remote insulin titration is clinically effective, feasible, satisfactory, and cost saving for low-income patients in a busy, urban clinic.

**Trial Registration:**

Trial Registration: Clinicaltrials.gov NCT01879579; http://clinicaltrials.gov/ct2/show/NCT01879579 (Archived by WebCite at http://www.webcitation.org/6WUEgjZUO).

## Introduction

### Background

Diabetes disproportionately affects the poor and uninsured, who are more likely to suffer the severe health consequences of uncontrolled diabetes, including heart disease, death, stroke, blindness, renal failure, and nontraumatic lower limb amputations [1].

Diabetes care is quite complex. Patients often need to learn self-management (eg, monitoring home blood glucose), make multiple lifestyle changes (eg, diet, exercise), follow complex medication regimens, and attend multiple clinic appointments (eg, primary care providers, diabetic educators, specialists). In public hospitals and clinics that serve low-income populations, these appointment slots can be few and often occur during patients’ work hours. Patients have to miss work, make arrangements for the children in their care, and arrange transportation to the clinic. These logistical and cost-related barriers to accessing clinic care contribute to the socioeconomic disparity in diabetes management [2,3,4,5].

Bellevue Hospital Center, located in New York City (NYC), primarily treats low-income, ethnically diverse patients [6]. The prevalence rate of diabetes in the hospital’s Adult Primary Care Center (APCC) is 15%, compared to the rate of 10.5% in NYC and 9% in the US (hospital prevalence rate obtained from internal hospital database, HHC Patient Registry for Proactive Care) [6]. Many of these patients are advised to start insulin therapy, in accordance with the standard for diabetes care. Proper insulin treatment involves multiple steps, including the need for patients to communicate blood glucose values to a clinician who then adjusts the patient’s insulin dose accordingly. Traditionally, this exchange of blood glucose data is achieved through face-to-face appointments with a clinician [7-11]. Given the many challenges low-income patients face attending frequent appointments, patients may struggle to have their insulin titrated regularly and the process of optimizing their dose is prolonged [9,12].

Mobile technology, especially mobile phones, may help alleviate the logistical barriers to care. Currently, 90% of US adults own a mobile phone, and 58% own mobile phones with advanced operating systems (smartphones). While only 47% of low-income adults own an advanced mobile phone, 84% of low-income adults own any mobile phone (basic or advanced) [13]. Text messaging and voice calls are available on most basic mobile phones, making interventions using basic mobile phone technology a viable option for low-income populations.

Several studies have used text messaging to help patients manage their diabetes care, even among low-income populations [8,14-18]. Text messages have been used successfully to remind patients to carry out self-care (eg, monitoring home blood glucose levels) and to transmit this data to the clinician, thus ensuring that a home blood glucose log is available at the time of the next in-person visit. We also found studies where clinicians adjusted insulin doses remotely. In these studies, patients sent their blood glucose values to their clinicians by accessing the Internet. Clinicians could respond by uploading their advice via the Internet or through text message. These studies demonstrate the feasibility of the remote exchange of both blood glucose values and insulin dosage advice. However, they required patients to have access to the Internet and, in some cases, to navigate a website [8,17,19].

The Mobile Insulin Titration Intervention (MITI) incorporates the strengths of the studies above by using text messages as a prompt to remind patients to check their home blood glucose values and by allowing the remote exchange of actionable data, namely the receipt of the values and the transmission of titration advice. MITI builds upon the above studies by tailoring these interventions to low-income patients, requiring only texting capabilities to send the blood glucose values and a simple phone call to receive titration instructions. This intervention requires only a low-cost, basic-feature mobile phone, not an advanced mobile phone or Internet access, which our patients often do not have.

We designed the intervention to include both text messages and phone calls for insulin titration, rather than one or the other. Text messages act as a reminder to patients to check their blood glucose levels and can be automated to be sent to the patient at a given time of day. Text messaging also provides a simple and quick way for patients to send their blood glucose data to the clinician from any location, given their phones are able to send text messages. We included phone calls for the adjustment of the insulin dose as a balanced approach between automated instructions (ie, insulin dosage sent via text, email, or Internet portal) and the personal nature of the in-person clinic appointment. Weekly phone calls give the patient an opportunity to discuss their treatment progress in real time with a clinician, while allowing the clinician to leave a voicemail with instructions if the patient is not available. This intervention is designed to alleviate the burden of in-person titration visits in a pragmatic manner, using basic technology available to our patient population.

### Objectives

The objectives of this study are to (1) evaluate if MITI is clinically effective by helping patients reach their optimal dose of insulin glargine (defined in the *Outcome Measures* section), (2) determine if the intervention is feasible within the setting and population, (3) assess patient satisfaction with the intervention, and (4) measure the costs associated with this intervention.

## Methods

### Overview

The MITI study is a randomized controlled trial to evaluate a mobile phone intervention for insulin glargine titration. This trial has been registered at ClinicalTrials.gov (NCT01879579). We will recruit patients from Bellevue Hospital Center’s Adult Primary Care Center who have type 2 diabetes and require insulin glargine titration. We will focus on glargine because it is the type of insulin used in our formulary. Using a parallel study design, patients will be randomized into either the MITI (intervention) arm or the usual-care (control) arm. Patients in the MITI arm will send their fasting blood glucose levels each weekday via text messages and have their insulin dose adjusted during phone calls with a diabetes nurse educator using a physician-approved algorithm. Patients in the usual-care arm will continue to receive their usual care, which includes scheduled clinic appointments to review daily blood glucose levels and to adjust their insulin dose. The primary outcome will be whether or not a patient reaches his/her optimal insulin glargine dose within 12 weeks.

### Setting

Bellevue Hospital Center is a large tertiary care hospital within New York City’s Health and Hospitals Corporation, the largest public hospital system in the United States and one of the largest safety-net providers. Bellevue Hospital’s APCC cares for an ethnically diverse patient population, where 71% of the patients are nonwhite (41% Hispanic, 24% black, and 6% Asian). In the APCC, 76% of outpatient clinic visits are for patients who are either uninsured (31%) or have Medicaid (45%) [6]. Patients in this study will be recruited from the APCC, where the prevalence rate of diabetes is 15%.

### Participants

We will recruit patients with diabetes who present to the Adult Primary Care Center. The inclusion criteria are as follows: (1) patients who are initiating insulin glargine treatment or require the titration of their existing insulin glargine dose, (2) English or Spanish speaking, (3) most recent hemoglobin A1c (HbA1c) value is ≥8%, (4) able and willing to inject insulin, and (5) able and willing to provide informed consent. We will exclude patients who meet the following criteria: (1) on short-acting insulin, (2) on systemic glucocorticoids, (3) with sustained serum creatinine of ≥1.5 mg/dL for men and ≥1.4 mg/dL for women, (4) with documented hypoglycemia unawareness, and (5) diagnosed with type 1 diabetes.

### Outcome Measures

The primary outcome will be whether or not a patient reaches his/her optimal insulin glargine dose within 12 weeks of enrolling in the study. Optimal insulin glargine dose is defined as the dose at which the patient has at least one fasting blood glucose value within the range of 80 to 130 mg/dL inclusive, or the maximum dose that can be safely administered to the patient. The research staff will record whether a patient has reached their optimal insulin dose at the time of the patient’s weekly titration phone call (if in the MITI arm) or clinic appointment (if in the usual-care arm).

We hypothesize that the MITI arm will have a greater proportion of patients who reach their optimal insulin dose than the usual-care arm. Other clinical effectiveness outcomes include the time taken to reach optimal dose, the incidence of hypoglycemia, and the change in HbA1c levels between baseline and 3 months.

Feasibility measures include patients’ text message response rate, ability of the diabetes nurse educator to reach patients for insulin titration, and the time spent by the diabetes nurse educator on the intervention.

We will measure patient treatment satisfaction at baseline and 3 months after study enrollment using the Diabetes Treatment Satisfaction Questionnaire. We will use an additional questionnaire—the “change” version of the Diabetes Treatment Satisfaction Questionnaire—to measure the change in the patient’s treatment satisfaction between baseline and 3 months [20]. We will also use a semistructured interview to gather qualitative feedback from patients in the MITI arm. This will be administered when the patient has completed the intervention—by reaching their optimal insulin dose or when 12 weeks elapse.  

We will collect data on the costs of insulin titration to compare the intervention to the established standard of care in the clinic. These outcomes include the time spent by patients traveling to the clinic, time spent in the waiting room prior to appointments, number and duration of insulin titration appointments, patient co-pays, and patient health care utilization (ie, the number of noninsulin-related medical clinic visits made at Bellevue during the 12-week study period).

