### Interventions

#### Usual-Care

Patients in the usual-care arm will continue with the treatment plan and appointments decided upon with their clinician prior to enrolling in the study (see Figure 1). According to the clinic’s current practice, a clinician reviews the patient’s fasting blood glucose log during appointments and titrates the insulin dose. Our research assistant (RA) will collect data, such as fasting blood glucose readings, insulin dosage adjustments, and appointment duration, from patients after appointments, in-person or by phone, as well as appointment duration from clinicians. These patients will continue to visit their primary care providers and have routine HbA1c tests according to the standard of care.

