#### Mobile Insulin Titration Intervention

Patients in the MITI arm will sign up for a Web-based health management platform in the clinic with the assistance of the research staff. The platform allows patients and clinicians to communicate via text messaging. Patients will receive a text message each weekday from the platform requesting the patient’ s fasting blood glucose level for that day. The messages will be automatically delivered each morning at a time prespecified by the patient, in either English or Spanish. Patients will respond via text message with their fasting blood glucose levels. Mobile phones can be provided to any patient who is otherwise eligible but does not have a mobile phone. It is implicit that a patient must be able to operate a mobile phone to participate in the study.

The diabetes nurse educator will check patients’ responses on the secure Web portal each weekday and call any patient reporting alarm values (ie, a blood glucose level <80 mg/dL or >400 mg/dL). Each Thursday afternoon, the diabetes nurse educator will call the patients to adjust their insulin dose according to a titration algorithm developed by physicians and nurses on the study team. The diabetes nurse educator may leave a voicemail with insulin titration instructions. If the patient cannot be contacted by phone, the diabetes nurse educator may call the patient’s emergency contact upon her discretion. Another clinician may check text responses and make titration phone calls if the diabetes nurse educator is not available. If Thursday is a holiday, the titration calls can take place on another weekday.

This protocol of weekday text messages and weekly phone calls will continue for up to 12 weeks (see Figure 2), until the patient reaches their optimal insulin dose, or the patient chooses to withdraw from the study. Patients may attend appointments with their primary care provider during the intervention, but will not need to attend appointments specifically for diabetes management (eg, high HbA1c clinic or diabetes nurse educator appointments) within the primary care clinic. After completing the protocol, the patient will be transferred back to usual care in the clinic. The research team will arrange for follow-up appointments with the patient’s primary care provider and, if appropriate, appointments with the diabetes nurse educator or high HbA1c clinic, so that the patient can resume their diabetes care through standard clinic visits.

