### Recruitment, Randomization, and Retention

We will recruit patients from the Adult Primary Care Center. Clinicians can alert the research study staff of any patient who is interested in the study and may be eligible (see Figure 3). The RA will also review the clinic’s electronic medical records to identify patients that may be eligible for the study. The RA will screen the patient for eligibility, explain the study, and provide them with a consent form to read and sign in person at the Adult Primary Care Center. All patients must provide informed consent before participating in the study protocol.

Since patients will be randomized sequentially at the time they provide informed consent, we will use block randomization (block size of 4) to make sure the number of patients in each arm is approximately balanced at any time point during the study. Patients will be stratified by whether the patient is initiating insulin therapy or having their existing insulin dose titrated. The random allocation sequence will be computer-generated by a coinvestigator and concealed in presealed envelopes. The patient’s arm assignment will be revealed to the patient and research team at the time of study enrollment by the RA. The research team and clinicians will not be blinded since the intervention requires that they alter the patient’s treatment plan or, in the case of the usual-care arm, collect data from clinicians and patients regarding their appointments.

At the time of enrollment, patients will receive a US $10 MetroCard to be used for travel to and from the clinic. Patients will receive a glucometer and a supply of test strips to ensure that they can test their blood glucose levels for the duration of the study. At approximately 12 weeks into the study, the research assistant will contact patients by phone to remind them to return to the clinic for their 3-month HbA1c blood test and complete the satisfaction questionnaire. Patients will receive an additional US $10 MetroCard.

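### The one-reading primary outcome is ascertained on a different schedule in each arm, so usual-care success can be under-recorded and the comparison can favour MITI without a difference in glycaemia

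*Protocol article*

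**What the plan says.** Outcome Measures lets a patient reach the optimal dose by either of two routes. The first is a glucose criterion: "at least one fasting blood glucose value within the range of 80 to 130 mg/dL inclusive". The other route needs no in-range value and is worded as follows: "or the maximum dose that can be safely administered to the patient". The primary outcome is whether this happens "within 12 weeks of enrolling in the study". Research staff record it at the "weekly titration phone call (if in the MITI arm) or clinic appointment (if in the usual-care arm".

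The two arms generate and review readings differently:

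- **MITI** (Mobile Insulin Titration Intervention): "Patients will receive a text message each weekday from the platform", and the nurse educator calls once a week, for up to 12 weeks. The Background section gives the purpose of the prompts: "Text messages act as a reminder to patients to check their blood glucose levels".
- **Usual care** (Usual-Care): patients keep the appointments agreed before enrolment, and the clinician reviews a home log at those visits. The research assistant collects readings and dose changes "from patients after appointments, in-person or by phone". No number of visits, prompting or minimum set of readings is stated.

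Recruitment, Randomization, and Retention adds, without limiting it to one arm, "Patients will receive a glucometer and a supply of test strips". The same section says that the research team and clinicians are not blinded. Follow-Up gives both arms a research assistant contact at about 12 weeks, for HbA1c and the satisfaction questionnaire but not for the primary outcome.

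**The concern.** With an at-least-one rule, the chance of success rises with every further reading that is taken and seen, even if the patient's glucose distribution stays the same. Here the number of readings and the number of recording occasions both depend on the arm. MITI has a prompt each weekday and up to 12 weekly reviews. Usual care has whatever the patient logs and whichever appointments are kept, and the Background section itself says these patients have difficulty attending frequent appointments.

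A usual-care success can therefore go unrecorded in two ways: the patient tests rarely, or there is no appointment at which the value can be seen. Both push the result towards the study hypothesis. The first objective is to show clinical effectiveness, and the primary test cannot separate better titration from more looking. The log-rank test of time to optimal dose (Data Analysis) has the same weakness, because success is dated at weekly calls in one arm and at appointments in the other.

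**Working it through.** **1. The plan's own figure.** Sample Size (Power Analysis) assumes 80% versus 50%, Fisher's exact test, two-sided 5% and at least 80% power. Exact enumeration gives power 0.796 at 43 per group and 0.802 at 44, so 44 is right. 44/0.9 = 48.9, which rounds up to 49 per group and 98 in total. The arithmetic is sound. The problem lies in how the outcome is ascertained.

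**2. Inputs.** From the article: 5 prompts a week × 12 weeks = at most 60 MITI readings, and 44 analysed per group. Assumed, because the article does not give them: 70% response to prompts (0.7 × 60 = 42 readings), 15 or 30 usual-care readings seen, and the chance that a reading is in range. Glycaemia is set equal in the two arms throughout.

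**3. Identical patients, independent readings.** With per-reading probability p and k readings seen, P(success) = 1 − (1 − p)^k.

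| p | MITI, k = 42 | Usual care, k = 15 | Gap (points) | Fisher rejects, 44 per group |
|---|---|---|---|---|
| 0.02 | 57% | 26% | 31 | 0.79 |
| 0.05 | 88% | 54% | 35 | 0.94 |
| 0.10 | 99% | 79% | 19 | 0.81 |

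Gaps are taken before rounding.

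**4. Patients who vary.** Patient mean glucose is taken as normal (mean 190, SD 35 mg/dL), with within-patient SD s. For each patient q = P(80 ≤ reading ≤ 130), and 1 − (1 − q)^k is averaged over patients.

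| s | Readings | MITI | Usual care | Gap (points) | Fisher rejects |
|---|---|---|---|---|---|
| 25 | 42 vs 15 | 44% | 33% | 11 | 0.14 |
| 35 | 42 vs 15 | 66% | 50% | 16 | 0.25 |
| 25 | 42 vs 30 | 44% | 40% | 4 | 0.04 |
| 35 | 42 vs 30 | 66% | 61% | 5 | 0.05 |

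With equal counts (42 vs 42) the rejection probability is 0.03. At 42 vs 30 the test therefore stays within its nominal 5%, while at 42 vs 15 it does not.

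**5. Missed appointments alone.** Let true success be 80% in both arms, and let a fraction m of usual-care patients have no appointment at which success can be recorded. The recorded usual-care rate is 0.80 × (1 − m).

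- m = 0.20: 0.80 × 0.80 = 64%, Fisher rejects with probability 0.30.
- m = 0.30: 0.80 × 0.70 = 56%, Fisher rejects with probability 0.60.
- m = 0.375: 0.80 × 0.625 = 50%, Fisher rejects with probability 0.80. This is the whole planned effect.

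**The case against.** Three points on the other side have force.

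First, a reader might infer that only readings taken at clinic visits count in usual care. The article does not say so. Appointments fix when the outcome is recorded, but the log reviewed there can hold weeks of home readings, and meters and strips are not restricted to MITI. If every usual-care patient kept a full log and had a visit near week 12, most of the bias in the binary outcome would disappear. This stands as a limit on the size of the bias. It does not remove the problem, because the article guarantees neither condition.

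Second, a reader might infer that a significant result would be pure artefact. That goes too far. The usual-care reading count is unknown, and the largest gaps need identical patients with independent readings, which is implausible in a group that mixes new starters with patients already on glargine. With varied patients and fairly full logs the gap is only 4 to 5 points.

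Third, more frequent contact is part of the intervention, and reaching a usable dose through more frequent review is a fair pragmatic aim for a pilot. More frequent titration may well have a real effect. Yet seeing more readings is not itself a clinical benefit, and this outcome counts it as one. HbA1c change at 3 months is less exposed, since both arms are reminded of the test at about 12 weeks, but it is a secondary outcome. The Discussion acknowledges lack of blinding and observer bias, but not unequal ascertainment.

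**Conclusion.** The concern holds in this form: the article fixes an at-least-one outcome with arm-specific recording occasions and no common set of readings, so following it as written can favour MITI at equal glycaemia. The direction follows from the design whenever fewer usual-care readings are seen or usual-care visits are missed. The size does not follow from the documents. Under the stated assumptions it runs from 4 to 5 points (42 vs 30 readings, varied patients), through 11 to 16 points (42 vs 15, varied patients), to 19 to 35 points (42 vs 15, identical patients), against a planned 30. Missed visits in 20% to 30% of usual-care patients would lower a true 80% to between 64% and 56%.

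The maximum-dose route adds a smaller point. It counts a patient who is never in range as a success, and the staff are unblinded. A reader might infer that this judgement is arbitrary. The article does not support that, since the titration algorithm is not shown and may set the maximum. Reporting by route is enough.

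**What to change.** 1. At the 12-week contact that both arms already have, the research assistant collects the stored glucometer or log fasting values for the whole 12 weeks, whether or not appointments took place. The primary outcome is classified from this common source, from a listing without arm.
2. Add a sensitivity analysis with the same number of readings per patient at the same scheduled times in both arms. Step 1 removes the dependence on appointments, but prompted patients may still have more readings.
3. Report the number of readings and of assessments by arm. Report success by route (in range or maximum dose), with an in-range-only analysis.
4. Keep the call- or visit-recorded outcome as supportive. For patients already past week 12, name unequal ascertainment as a limitation.

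A final-week window is not a simple substitute. It equalises the period but not the count: in the varied-patient model, 7 versus 3 readings still gives 25% versus 16% (s = 25) or 37% versus 23% (s = 35). It also replaces success at any time within 12 weeks by status at week 12. If it is chosen, the 50% and 80% in Sample Size (Power Analysis) must be restated.

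The cost is an amendment and a little research assistant time at an existing contact. Values will be missing for patients who do not return or have no stored readings. Recruitment has closed, so the change helps only patients still in follow-up or whose meters or logs can still be read. The clinical titration rule is unchanged.

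### The cost comparison is tilted toward a saving: titration staff time is a cost outcome in usual care, but MITI nurse time is only a described feasibility measure

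*Protocol article*

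**What the plan says.** Objective 4, in the Objectives section, is to "measure the costs associated with this intervention". The Conclusions of the Abstract go further: "We aim to show that remote insulin titration is clinically effective, feasible, satisfactory, and cost saving for low-income patients".

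Outcome Measures states what the cost data are for: "We will collect data on the costs of insulin titration to compare the intervention to the established standard of care in the clinic". It then itemises: "These outcomes include the time spent by patients traveling to the clinic, time spent in the waiting room prior to appointments", followed by the count and length of titration appointments, co-pays, and clinic visits unrelated to insulin. The same section places "the time spent by the diabetes nurse educator on the intervention" among the feasibility measures.

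Data Analysis gives titration appointments and health care utilization a between-arm t test or rank-sum test. Feasibility outcomes, travel time, waiting time and co-pays are only described.

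The Usual-Care section has appointment length collected from both patients and clinicians. The section on the intervention has the nurse educator check the portal every weekday, phone patients who report alarm values, and phone weekly to titrate, for up to 12 weeks. The arm also uses a Web-based platform and, for patients without a phone, a supplied one. MITI patients "will not need to attend appointments specifically for diabetes management".

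**The concern.** Titration takes staff time in both arms. In usual care it is spent in appointments; in MITI it is spent on portal checks and calls. The plan files the first under cost and the second under feasibility, and the analysis follows that split. Staff time that MITI removes is tested between arms, while staff time that MITI adds never enters the comparison.

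A second point compounds this. MITI patients have no need of the diabetes-management visits that make up usual-care titration, so fewer titration appointments in that arm are largely a consequence of the design. A small p-value there would be easy to read as evidence of a saving when the replacement work has not been set against it.

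At stake is objective 4. No listed cost outcome is a cost of delivering the intervention, and the stated aim of showing a saving would rest on the items that MITI was designed to reduce.

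**Working it through.** The document states no cost figure, so there is none to reproduce. Its only computed figure, the sample size for the primary outcome, plays no part here.

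**Step 1: classify the items.**

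| Item | Filed under | Analysis | Expected effect of the design |
|---|---|---|---|
| Travel time | Cost | Described | Falls in MITI |
| Waiting time | Cost | Described | Falls in MITI |
| Titration appointments (count, length) | Cost | Tested between arms | Falls in MITI |
| Co-pays | Cost | Described | Falls in MITI |
| Visits unrelated to insulin | Cost | Tested between arms | Not removed by MITI |
| Nurse-educator time on MITI | Feasibility | Described | Arises only in MITI |
| Platform, supplied phones | Not named | None stated | Arises only in MITI |

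Of the five named cost items, four fall largely by design and none is a cost of delivering MITI.

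**Step 2: could the nurse time matter?** From the intervention section, a full course has 12 × 5 = 60 weekday checks and 12 weekly calls. The times are assumptions, because the document gives none: 0.5 to 2 minutes per check, 5 to 15 minutes per call, and 20 to 40 minutes per clinic appointment. Alarm calls and voicemails are left out.

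Nurse minutes = weeks × 5 × minutes per check + weeks × minutes per call.

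- 12 weeks, low: 60 × 0.5 + 12 × 5 = 30 + 60 = 90.
- 12 weeks, high: 60 × 2 + 12 × 15 = 120 + 180 = 300.
- 4 weeks, low: 20 × 0.5 + 4 × 5 = 10 + 20 = 30.
- 4 weeks, high: 20 × 2 + 4 × 15 = 40 + 60 = 100.

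The 4-week case is included because the intervention stops when the optimal dose is reached, and the Sample Size section expects at least 80% of MITI patients to get there within 12 weeks.

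**Step 3: break-even.** The number of usual-care appointments is also not given, so the useful quantity is how many avoided appointments the nurse time equals (nurse minutes ÷ minutes per appointment).

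| Course | Nurse minutes | At 20 min | At 30 min | At 40 min |
|---|---|---|---|---|
| 12 weeks | 90 to 300 | 4.5 to 15 | 3 to 10 | 2.25 to 7.5 |
| 4 weeks | 30 to 100 | 1.5 to 5 | 1 to 3.3 | 0.75 to 2.5 |

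If MITI avoids fewer appointments than the break-even number, it uses more staff time; if it avoids more, it uses less. Both are plausible over these ranges.

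**The case against.** The strongest reply has four parts.

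- **Nurse time is measured.** So is usual-care appointment length, and a reader could set one against the other. This stands, and it narrows the point: the data exist, but the plan keeps them out of the cost comparison.
- **The list is open and the article is condensed.** The cost items are introduced as included outcomes, and unit costs, perspective and platform fees may be set out in a fuller document. This stands for the platform and phones, where the article is merely silent. It does not answer the nurse-time point, because the article places that item explicitly, and outside cost.
- **The claim may be about patients only.** The Background stresses missed work, childcare and transport, and the Abstract speaks of low-income patients. That reading is reasonable. However, the cost list also contains clinic resources, and objective 4 is not limited to the patient side. The perspective needs stating.
- **A saving is not guaranteed.** A reader might infer that the result is built in, that the comparison can only favour MITI, or that the appointment test merely tests allocation. The documents do not support this. Visits unrelated to insulin are counted and could rise. MITI patients may still see their primary care provider. Implementation Challenges reports that some patients with prepaid phones kept attending in person for titration. Usual-care patients may attend few visits, so the size of any reduction is an empirical matter. No total-cost or cost-saving test is specified.

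**Conclusion.** The concern holds as a tilt in the cost comparison, not as a predetermined result. The same resource, staff time for titration, is a tested cost outcome in one arm and a described feasibility measure in the other, and no cost of delivering MITI is named. As listed, the outcomes do not answer objective 4 and do not support an unqualified cost-saving conclusion.

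The size cannot be fixed from the document. The 90 to 300 nurse minutes for a full course, and 30 to 100 for a 4-week course, rest wholly on assumed times. They show that the omitted item is large enough to offset the appointment time saved, not that it does. A reader might infer that MITI uses as much staff time as usual care or more; neither direction can be established.

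This is a minor point for a secondary objective of a pilot. The primary outcome and the sample size are unaffected.

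**What to change.** Carry the recorded nurse-educator time (portal reviews, alarm calls, titration calls) into the cost outcomes. Compare total titration staff minutes per patient between arms over the same 12 weeks, counting in both arms any titration visits that take place, including those of MITI patients after return to usual care. List platform and supplied-phone costs alongside. Keep the comparison of appointment counts if wanted, but say that it is not by itself evidence of a saving.

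If this is not done, limit the cost conclusion explicitly to patient travel, waiting time, co-pays and clinic visits.

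The cost is small, because nurse time is already collected. Whether platform and phone expenditure was recorded is not stated and would have to be confirmed. Wage valuation, bootstrap intervals and collection of patients' text charges are not needed for this purpose. The downside is that the cost result may be less favourable to MITI.
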